### 3.3. Parents

#### 3.3.1. Parent Survey

Parents completed a 10 to 15-min survey at baseline with questions pertaining to themselves and their child, to better understand how children engage in active outdoor play and the factors potentially involved. The first section of the survey gathered information on parent demographics, physical activity participation (parent and child), sleep (child), sedentary behavior (parent), and parent perceptions of their child’s physical literacy. Parent perceptions concerning the level of risk associated with children’s physical activity/play behavior, and affordances for risk taking during physical activity/play, were also assessed. A total of 85 families completed the parent survey; 76 from the original cohort, and 9 from the new cohort.

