### Study Objectives

The objectives of this research were to evaluate the efficacy of the loose parts intervention versus outdoor play practice in standard early child care settings to:(1)improve children’s physical literacy, and increase time in PA and active outdoor play;(2)improve educators’ attitudes, beliefs, perceived competency, and intentions towards incorporating the intervention into practice;(3)increase parents’ and educators’ understanding of play in child health and development.

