#### 3.3.2. Parent Interviews

At the end of the 6-month intervention, a subsample of parents in the intervention and control groups was invited to participate in parent interviews. Each director was asked to recommend two to four parents who might be willing to continue their involvement in the PLEY project and these parents were then invited to participate. The interviews were conducted by a facilitator and audio-recorded, with the assistance of a note-taker at 10 sites with 18 parents (individually or in small groups). The semi-structured interviews asked questions related to a typical day for their child both indoors and outdoors with a focus on active outdoor play, and explored the who, what, when, and where, of active outdoor play. Interviewers probed whether changing seasons and inclement weather influenced play decision-making. There was an overall interest in discovering what the parents learned about the project, about physical literacy and about the role of active outdoor play in their child’s healthy growth and development through participation in the PLEY project. Finally, there was an interest in learning about parent attitudes towards risk taking during play and seeing if those attitudes have an influence on parenting behaviors.

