## 4. Discussion

As the purpose of this paper is to describe the purpose, study design and methodology of the PLEY loose parts intervention, no results are included in this paper. It is hypothesized that children in centres exposed to the loose parts intervention will experience greater increases in physical literacy, PA and active outdoor play than the usual practice centres. Previous studies similar to this have reported changes (mean(95%CI)) of −0.2(−1.7 to 1.3) in physical activity between groups [53], and 2.5 (−1.7 to 6.7) in the sum of scores for fundamental movement skills between groups [40]. It is also hypothesized that parents and educators involved in the intervention centres will gain a greater understanding of physical literacy, PA, and active outdoor play. It is hypothesized that educators will be exposed to an increase of risk-taking behaviors with the introduction of loose parts into outdoor play environments and that they will begin to recognize their children’s ability to assess risk independently. Finally, it is also hypothesized that the loose parts intervention has the potential to clarify the role of the educator as a guide, a mentor and a co-player in outdoor environments.

This study consists of various strengths and limitations to be acknowledged. The major strength of this study lies in the uniqueness of an outdoor play intervention with the use of loose parts, the inclusion of urban, suburban, and rural regions of Nova Scotia, and in the measurement of child, parent and educator components. The limitations of this study include the dropout rate of children, which resulted in a lower sample size during the post-testing, and that not all components of physical literacy were measured as part of this study, given the age of the child.

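### Single end-of-study interviews with 18 director-recommended parents cannot determine whether the intervention increased parents' understanding of play

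*Protocol article*

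**What the plan says.** The Study Objectives section places all three objectives under one comparative aim, to "evaluate the efficacy of the loose parts intervention versus outdoor play practice in standard early child care settings". The third is to "increase parents’ and educators’ understanding of play in child health and development". Section 4 (Discussion) adds a directional hypothesis that "parents and educators involved in the intervention centres will gain a greater understanding of physical literacy", as well as of physical activity and active outdoor play.

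Two parent instruments are described.

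- **Survey (section 3.3.1).** "Parents completed a 10 to 15-min survey at baseline with questions pertaining to themselves and their child". The listed content is demographics, parent and child activity, child sleep, parent sedentary behaviour, "parent perceptions of their child’s physical literacy", and perceptions of risk and of affordances for risk in play. "A total of 85 families completed the parent survey; 76 from the original cohort, and 9 from the new cohort".
- **Interview (section 3.3.2).** It was held once, at the end of the six-month intervention, and parents in both arms were invited. On selection: "Each director was asked to recommend two to four parents who might be willing to continue their involvement in the PLEY project". Interviews took place "at 10 sites with 18 parents (individually or in small groups"). Among other topics, they explored what parents had learned through the project.

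Section 3.4 (Data Analysis) then says that the educator focus groups and parent interviews will be analysed qualitatively to establish whether the intervention raised parents' and educators' understanding of play.

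**The concern.** Saying that an intervention increased something needs either a measure before and after, or a comparison of randomized groups whose measured members still represent those groups. The parent strand has neither. The interview has no earlier counterpart, and its participants were chosen after allocation on a criterion, willingness to stay involved, that the intervention could itself affect.

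At stake is a conclusion that the article has already framed. If the themes from these interviews are reported as the answer to objective 3, a reader will take them as evidence of efficacy in parents, with the authority of a randomized trial behind them. The interviews can show what some willing parents said they had learned. They cannot show that the intervention caused it, or that control parents learned less.

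**Working it through.** The article gives no sample size, effect size or power for the parent objective, so there is no design figure to reproduce. The check sets the claim beside the data and counts the coverage.

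**1. Is any measure of parents' understanding taken twice?**

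| Instrument | When | Covers understanding of play, as described? |
|---|---|---|
| Parent survey (3.3.1) | Baseline | No |
| Parent interview (3.3.2) | End of intervention | Yes, as self-reported learning |

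Section 2.2.1 says in general terms that quantitative and qualitative data were collected at baseline, 3 months and 6 months. The parent sections give one time point each, whereas the child measures (3.1.1) and the educator focus groups (3.2.4) have their repeats spelled out. Parents described as having the same measure of understanding at two times: none. Change within parents cannot be estimated.

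**2. Can the arms be compared at study end?**

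A comparison at the end only would be legitimate if those interviewed represented the randomized arms. Intervention centres had received kits and training, and control centres received kits only at the end (2.2.1, 3.2.3), so directors would have known their centre's arm when they recommended parents. Selection therefore followed allocation and was not blind to it.

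**3. Coverage**

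- Survey: 76 + 9 = 85 families, which agrees with the stated total. 85 / 183 = 46% of children measured at baseline, if there was one child per family.
- Interview: 18 / 183 = 9.8% of children, on the same footing.
- Sites: 10 / 19 = 53%, with 18 / 10 = 1.8 parents per site.
- If all 19 directors had recommended two to four parents, there would have been 19 × 2 = 38 to 19 × 4 = 76 names. The 18 interviewed are 18 / 76 = 24% to 18 / 38 = 47% of that.
- The text does not split the 18 parents or the 10 sites by arm. With 11 intervention and 8 control centres, the 10 sites could include anywhere from 10 − 8 = 2 to 10 intervention centres, ignoring the one centre that dropped out.

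**4. Conclusion of the check**

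Step 1 rules out an estimate of change. Steps 2 and 3 rule out a fair between-arm comparison. What is left is a descriptive account of what selected parents reported.

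**The case against.** The strongest reply is that this is a qualitative strand and should be judged as one. Purposive selection is common in interview studies, asking people what they learned is a recognised way to record perceived change, both arms were invited, and every director received the same request. All of this stands, and it supports reporting the interviews as description. It does not support using them to establish that the intervention increased understanding relative to standard practice. An identical request in both arms does not make the groups comparable, because willingness to stay involved may mean something different in a centre that has had the kits and training than in one still waiting for them.

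Some stronger readings are tempting but are not supported:

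- *That the survey was the intended outcome measure and should have been repeated.* The article never assigns it to objective 3. Its stated purpose is to understand how children engage in active outdoor play and what influences this. Repeating it unchanged would measure perceptions of the child and of risk, which is a different construct.
- *That setting child data beside baseline survey responses is an error.* Baseline parent characteristics are ordinary correlates of child outcomes.
- *That only intervention parents were approached, or that the interviews are bound to show an increase.* Both arms were invited, and neither the direction nor the size of any bias can be read from the document.
- *That the flaw reaches the main results.* Section 2.2 limits the primary aim to children's outcomes.

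**Conclusion.** The point holds as a mismatch between claim and data. The Study Objectives, section 3.4 and the Discussion together promise a finding about an intervention effect on parents' understanding. The only data bearing on it are single interviews with 18 director-recommended parents at 10 of 19 centres, with no baseline measure of the construct. Neither change nor a fair between-arm difference can be determined.

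This rests on the parent sections being complete as to time points, on the survey content being as listed, and on directors knowing their centre's arm, which follows from the kit and training arrangements but is not stated in so many words. The percentages against 183 assume one child per family and one interviewed parent per child. The conclusion does not depend on them.

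The consequence is limited to the parent half of a non-primary objective. The educator half was not assessed here. It is worth correcting because the article fixes the data source, the route of selection and the conclusion to be drawn, so this is not a detail left to an analysis plan.

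**What to change.** Data collection is reported as finished in September 2018, but the analysis is written in the future tense, so the change is to wording and reporting:

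1. In the Study Objectives, separate the parent part of objective 3 and restate it as describing parents' views and self-reported learning about play at study end.
2. In section 3.4, say that the parent interviews will be analysed thematically for that purpose, and remove the statement that they will establish an effect of the intervention on parents.
3. In the Discussion, replace the hypothesis of a greater gain among parents in intervention centres with the same descriptive aim.
4. When reporting, give the number of interviewed parents and sites by arm, state that directors recommended the parents after allocation and on what criterion, and make no claim of an intervention effect on parents' understanding.

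The cost is a few sentences and one count by arm, with no new data. The downside is that the parent part of objective 3 becomes descriptive and no longer supports an efficacy statement. The child analyses need no change.

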#### 3.3.2. Parent Interviews

At the end of the 6-month intervention, a subsample of parents in the intervention and control groups was invited to participate in parent interviews. Each director was asked to recommend two to four parents who might be willing to continue their involvement in the PLEY project and these parents were then invited to participate. The interviews were conducted by a facilitator and audio-recorded, with the assistance of a note-taker at 10 sites with 18 parents (individually or in small groups). The semi-structured interviews asked questions related to a typical day for their child both indoors and outdoors with a focus on active outdoor play, and explored the who, what, when, and where, of active outdoor play. Interviewers probed whether changing seasons and inclement weather influenced play decision-making. There was an overall interest in discovering what the parents learned about the project, about physical literacy and about the role of active outdoor play in their child’s healthy growth and development through participation in the PLEY project. Finally, there was an interest in learning about parent attitudes towards risk taking during play and seeing if those attitudes have an influence on parenting behaviors.

### 3.4. Data Analysis

Descriptive statistics will be used to describe study participants (children, educators, parents) and participating child care centres. Linear mixed models with a random effect for centre will be used to determine if children exposed to the PLEY intervention had greater increases in physical literacy, PA, and time in active outdoor play, compared to children in the usual care group (control group). The model will include variables from the children’s TGMD-3 scores, PGMQ scores, and physical activity (as determined by accelerometry). The analysis will be approached from an intention-to-treat strategy. One of the primary outcome measures will be physical activity differences between the groups, while secondary outcomes include height, weight, BMI, and age. Additional analyses of the variables may include an analysis of covariance (ANCOVA) to determine differences in TGMD and PGMQ scores, with similar secondary outcomes of height, weight, BMI, and age, and again including a random effect to control for the clustered design. Missing data will be controlled for within the selected models and analyses. Significance level for these analyses will be set a *p* < 0.05.

Educator focus group data, and parent interview data, will be explored using qualitative analyses, to determine whether the intervention improved educators’ attitudes, beliefs, perceived competency, and intentions towards incorporating the intervention into practice; and increased parents’ and educators’ understanding of play in child health and development. These qualitative data will be transcribed and analyzed using NVIVO software to identify emerging themes. Children’s physical literacy and PA data will be examined in comparison with parent survey and interview responses, and educator survey and focus group responses, using a mixed methods approach. Data from the RE-AIM framework analysis and qualitative data emerging from the photo elicitation focus groups with intervention sites will determine the effectiveness of the intervention to achieve desired outcomes. The mixed methods approach will provide a more holistic understanding of the impact of the PLEY intervention on children’s physical literacy. Although the child measures only include some domains of physical literacy (e.g., physical competence and daily behavior) other aspects of the study including educator focus groups allow us to obtain data on the other components of physical literacy.

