## 2. Experimental Design

### 2.1. The Intervention

The Physical Literacy in the Early Years (PLEY) project is a randomized, mixed-methods, controlled trial focused on improving physical literacy, PA and active outdoor play in Nova Scotia preschoolers aged 3 to 5 years, through the integration of loose parts materials into outdoor play spaces in regulated child care centres. The PLEY project uses a Socio-Ecological approach [37] to address multiple levels of influence such as the intrapersonal, interpersonal, organizational, community, physical environment, and political levels. An internationally recognized socio-ecological framework, the RE-AIM framework (reach, effectiveness, adoption, implementation, and maintenance) [38], is used to examine research translation and dissemination, and evaluate the intervention. The RE-AIM framework evaluates the ‘reach’ to the target population; the ‘effectiveness’ of the intervention; the extent of ‘adoption’ of the intervention in child care centres; implementation; and ‘maintenance’ of the intervention effects. The RE-AIM framework for centre, educator and child levels is highlighted in Figure 1. This framework approach allows for the possibility to inform current policy and practices in Nova Scotia child care centres at the different levels impacted. This trial was retrospectively registered in October 2017 with BioMed Central under the trial registration number ISRCTN14058106.

The PLEY project was developed using an interdisciplinary, multi-sectoral partnership of researchers, practitioners (early childhood educators), government and policy-makers. The practitioner lens is critical to the partnership, as it provides a deeper understanding of the typical processes that take place in child care centres on a day-to-day basis and gives insight into optimal ways in which the intervention and research can be successfully conducted.

The goal of the PLEY project is to encourage and enable early childhood educators to integrate loose parts materials into child care centres’ outdoor play spaces as a means of improving preschoolers’ physical literacy and increasing time in PA and active outdoor play. The intervention is composed of seven components, which are detailed in Figure 2.

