#### 2.2.1. Study Design

A total of nineteen (19) child care centres across Nova Scotia (spread across over 240 km) were randomly allocated to either the intervention (n = 11) or control (n = 8) group. The study took a staggered approach to the recruitment of child care centres. Sixteen sites (intervention: n = 8; control: n = 8) were recruited in November/December of 2016 (Phase 1). An additional three intervention sites were recruited in November of 2017, to account for the drop-out of 1 centre in October of 2017, and participant (child) withdrawal. This study adheres to the CONSORT guidelines for randomized trials. Quantitative and qualitative data were collected at baseline, 3 months, and 6 months post-intervention. Quantitative data were collected from 183 participants at baseline through movement assessments and accelerometry. The same assessments occurred at 3 months post intervention and 6 months post intervention. Centres in the intervention group were provided with a loose parts kit to incorporate in their active outdoor play. The other centres were asked to maintain current scheduling of outdoor play and related activities and received a loose parts kit at the end of the intervention. The loose parts kits for the PLEY project intervention were intended for the outdoor environment and included: buckets and lids (variety of shapes and sizes), rope and pulley, tree cookies, milk crates, a package of hose tube, 20+ balls; a variety of sizes and weights, wood pieces, a bread tray, large cardboard tubes, funnels of different sizes, a tarp, 5′ planks, 5′ PVC tubing (4” and 2” diameter), rocks, and tires. The contents of the loose parts kits were determined based on consultation with the existing literature and discussions with early childhood educators to select natural and synthetic loose parts that best suited the purposes of this project.

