## 3. Procedure

### 3.1. Children

#### 3.1.1. Demographic and Body Composition

Demographic data, including age and sex, and physical characteristics, including height and weight, were taken by trained personnel at child care centres. Height was assessed using a portable stadiometer (SECA, Hamburg, Germany) and taken to the nearest 0.1 cm. Weight was assessed using a digital scale (A&D Medical, Milpitas, CA, USA) and taken to the nearest 0.1 kg. Children’s height and weight were measured with children wearing light clothing and no footwear. The height and weight of each child were used to determine Body Mass Index (kg/m^2^), which will be interpreted using z-scores. Data were collected at baseline, and at 3- and 6-months post-intervention.

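### Age is listed as a secondary outcome of the physical activity analysis and again of the possible ANCOVA, although the intervention cannot change it

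*Protocol article*

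**What the plan says.** Section 3.4 (Data Analysis) plans linear mixed models with a random centre effect to compare increases in physical literacy, physical activity and active outdoor play between arms. It makes physical activity one of the primary outcomes and continues: "while secondary outcomes include height, weight, BMI, and age".

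It then adds an optional analysis: "Additional analyses of the variables may include an analysis of covariance (ANCOVA) to determine differences in TGMD and PGMQ scores". The same sentence goes on "with similar secondary outcomes of height, weight, BMI, and age". The second analysis is therefore only a possibility, but the label given to age is the same in both sentences.

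Section 3.1.1 describes the same variables differently: "Demographic data, including age and sex, and physical characteristics, including height and weight, were taken by trained personnel at child care centres". It schedules data collection at baseline and at 3 and 6 months, and says that BMI will be read through z-scores.

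The study objectives (section 1) and the hypotheses (section 4) mention no effect on age.

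**The concern.** A secondary outcome is something that the intervention might change. Age advances at the same rate in both arms whatever is placed in the play space. If the sentence is followed literally, age is compared between arms at the 5% level and the result is reported among the trial's effects, where it has no meaning as an effect.

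The useful place for age is on the other side of the model. Section 3.1.2 builds the movement-skill score as a sum over skills, and section 2.1 defines the population as "Nova Scotia preschoolers aged 3 to 5 years". Over that range age is a natural candidate predictor of a summed skill score. The only role that the analysis section gives it is that of an outcome, and an analyst working from this text could not tell whether adjustment was intended.

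**Working it through.** The plan gives no figure to reproduce. The check sets the statements about age side by side and then asks what a comparison of age could estimate.

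**Where age appears**
- Section 3.4, physical activity analysis: secondary outcome.
- Section 3.4, possible ANCOVA of TGMD and PGMQ scores: secondary outcome again. The repetition makes an isolated slip unlikely.
- Section 3.1.1: demographic data, alongside sex.
- Sections 2.1 and 2.2.2: the eligible range, 3 to 5 years.
- Section 2.2.2, allocation: only rural or urban location is mentioned; age is not a stratification factor.
- Named as a covariate: nowhere.

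**What a comparison of age estimates**
1. For each child, age at follow-up = age at baseline + time elapsed. Neither term on the right contains a treatment effect.
2. Averaged by arm, the difference in mean age at follow-up = the difference in mean baseline age among children still measured + the difference in mean elapsed time.
3. The first part is baseline imbalance, as modified by any drop-out that differs between arms. The second is assessment timing.
4. The mixed models are aimed at increases. The increase in age is exactly the elapsed time, so such a model for age would test only whether visits were timed alike in the two arms.

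**Why baseline age still deserves a place in the models**
- The units allocated are few: 11 intervention and 8 control centres, 19 in all (section 2.2.1).
- Balance on age rests less on randomization for the late sites, because all of them are in one arm: "An additional three intervention sites were recruited in November of 2017".
- Section 4 acknowledges that child drop-out reduced the post-test sample.

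These facts show that age imbalance is possible. They do not show that it occurred.

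**Cost of adjustment**
- Baseline age as a linear term: 1 degree of freedom.
- Sex: 1 degree of freedom.
- Total: 1 + 1 = 2, against 183 children at baseline (2/183 = 1.1%).

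**The case against.** The strongest reply is that this is a condensed article with a probable slip of terminology. The authors may well have meant covariates, and the choice of covariates is commonly left to an analysis plan that is not shown. Part of this stands: the absence of a covariate list is not an error here, and it cannot be said that age lost a covariate role, because the article never gave it one. The reply does not rescue the label, however. A separate plan could add covariates, but it could not make age a valid efficacy outcome.

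Four stronger readings are tempting and are not supported.

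- **All four listed variables are meaningless outcomes.** Height, weight and BMI are measured at three time points, and the introduction links physical activity to adiposity. They can be secondary outcomes without appearing among the hypotheses.
- **The list carries an 18.5% chance of a spurious finding.** That is 1 - 0.95^4 = 0.185, which needs four independent true null hypotheses. BMI is calculated from height and weight, so independence fails by construction, and three of the four are legitimate outcomes.
- **Leaving age out inflates the variance by 25 to 67%.** If age explained 20 to 40% of the score variance, 1/(1 - 0.2) = 1.25 and 1/(1 - 0.4) = 1.67. Those percentages are assumptions with no source in the documents, and the result applies to an unadjusted comparison of post-intervention scores. The article plans models for increases, and possibly ANCOVA. A child's baseline score already carries much of the influence of age.
- **The BMI entries conflict.** Section 3.4 says BMI, not raw BMI, and can be read as shorthand for the z-score approach in section 3.1.1.

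**Conclusion.** The point holds for age. It is wrongly classed as a secondary outcome in both sentences of section 3.4, at odds with its treatment as demographic data in section 3.1.1. This conclusion needs no numerical assumption, because it follows from what age is.

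The direct consequence is small: one comparison at the 5% level, in each place where age is listed, that cannot be read as an effect. A reader might go on to infer that the skill or activity comparisons are biased by age-related drop-out. The documents do not show this. It would require drop-out that is related to age, that differs between arms, and whose influence remains after baseline scores are used.

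The correction is still worth making. The label is plainly wrong, and the remedy uses data already collected. Adjustment would add some precision and guard against age imbalance across 19 centres. How much precision cannot be stated from the documents, and the gain shrinks where the baseline score is already in the model.

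**What to change.** 1. Remove age from the secondary outcomes in both sentences of section 3.4.
2. State that baseline age and sex enter the child-level mixed models, and any ANCOVA of TGMD and PGMQ scores, as fixed covariates.
3. Say which role height, weight and BMI have. They may stay as secondary outcomes, with BMI analysed as the z-score of section 3.1.1. If covariates were meant, use only their baseline values, because the 3- and 6-month measurements follow allocation and could themselves be affected by the intervention.

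The cost is a change of wording and about two child-level degrees of freedom. No new data are needed, since section 3.1.1 already collects age and sex. Section 2.2 places the end of data collection in September 2018, so the change should be dated and disclosed as a correction to the published plan.
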